#### Evaluation of risk factors for aneurysms

Multiple regression analysis will be used to calculate OR values for high risk factors, including life habits and clinical and epidemiological data. Confidence intervals of 95% and cut-off values for sensitivity and specificity for predicting occurrence of an aneurysm rupture will be determined by receiver operating curves (ROCs). Next, the model will be used to assess risk of aneurysm rupture in the validation group and thus determine the model’s efficacy and accuracy. Finally, the model will be adjusted as indicated and established.

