**Methods:**

The China Intracranial Aneurysm Project-2 (CIAP-2) will comprise screening of a cohort of 500 patients with UIA (From CIAP-1) and focus on hemodynamic factors, high resolution magnetic resonance imaging (HRMRI) findings, genetic factors, and biomarkers. Possible risk factors for rupture of UIA, including genetic factors, biomarkers, HRMRI, and hemodynamic factors, will be analyzed. The first project of the China Intracranial Aneurysm Project (CIAP-1; chaired by the Department of Neurosurgery, Tangdu Hospital, Fourth Military Medical University, Xi’an, Shaanxi, China) will prospectively collect a cohort of 5000 patients with UIA from 20 centers in China, and collect baseline information for each patient. Multidimensional data will be acquired in follow-up assessments. Statistically significant clinical features in the UIA cohort will also be analyzed and integrated into the model for predicting risk of UIA rupture. After the model has been set up, the resultant evidence-based prediction will provide a preliminary theoretical basis for treating aneurysms at high risk of rupture.

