### Data collection and management

The following patient characteristics will be collected and recorded: (1) basic clinical characteristics; (2) relevant data concerning personal and family history; (3) relevant imaging findings; (4) findings of head HRMRI, computational fluid dynamics (CFD) testing, and relevant genetic testing; (5) relevant laboratory findings; and (6) neurological function-related scores on admission or first visit. The following characteristics of aneurysms will be collected and recorded: size, neck size, dome-to-neck ratio, dome-to-artery ratio, shape, location, clinical presentation, and number of aneurysms.

The follow-up data collected will comprise: (1) frequency and number of follow-up assessments; (2) findings on general evaluation; (3) deaths; (4) imaging findings; (5) UIA growth (assessed by repeated imaging to avoid treatment bias); and (6) life-style changes. Throughout, neurobehavioral-related scores will include: (1) Glasgow Coma Scale scores; (2) improved RANKIN scale scores (somatic changes); and (3) Mini-Mental State Examination scores (psychological changes).

The participants will initially be followed up three times: at 90 ± 14 days, 180 ± 30 days, and 365 ± 30 days and at least annually for a minimum of 5 years thereafter. Participation in the study will end if rupture occurs. Patients with SAH will be transferred to the CIAP-5 project (a study of emergency treatment of aneurysmal subarachnoid hemorrhage; CIAP-5, the fifth project of the China Intracranial Aneurysm Project, is managed by Xuanwu Hospital, Capital Medical University, Beijing, China). In addition, patient’s relatives are requested to report sudden deaths to the study group. In such instances, autopsies will immediately be organized in study hospitals and tissue samples of ruptured aneurysms will be supplied to the project for analysis, subject to the informed consent of the participants’ relatives.

Formal training, including investigator training and familiarization with the study protocol, will be initiated. An inspection team of experts drawn from various organizations will follow participants up with the specified regular monitoring until the end of the study period. All data will be collected on paper Case Report Forms (CRF), then input into Electronic Data Capture (EDC) for management, and retained for 5 years after the end of the study. The accuracy and rigorousness of the data will be checked in a timely manner.

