This study will incorporate nested screening of 500 individuals from cohort 1 (CIAP-1). Recruitment for this study started in September 2016. The estimated primary completion date will be in December 2020. The project will produce preliminary results in the 5th year. After the end of the 5th year, we will have a longer follow-up visit to the patients who have been in the group.

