## Statistical methods

### Total sample size

CIAP-1: Calculation of the required sample size using an expected annual rupture rate of 1%, allowable error of d = 0.6%, and alpha = 0.05 on two-sided testing indicated that 1173 patients need to be enrolled per year, that is, 4692 over 4 years. An annual rupture rate of 1% [2] results in a loss rate of less than 20%. A reported hemodynamic index (complex flow patterns OR = 4.7) and HRMRI index (aneurysmal wall enhancement OR = 3.05 for ruptured versus unruptured aneurysm) also indicate that this sample size would be sufficient [12, 43]. Given that genetic factors have not yet been evaluated [35], our genetic testing will assess previously reported possible genetic indicators of prognosis; additionally, target genes and biomarkers will be selected according to the latest research progress in the future. In the 5th year of the study, we will analyze the data. As previously mentioned, at least 130 aneurysms are expected to rupture in the modeling group in the first 4 years. Allowing for a loss rate of 20%, the study will need to enroll 500 individuals.

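### Rupture is analysed as a yes/no outcome with odds ratios and plain ROC cut-offs although follow-up differs between patients by design, so predictions have no time horizon and odds ratios are biased when a predictor is linked to time at risk

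*Protocol article*

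**What the plan says.** Under Evaluation of risk factors for aneurysms, the protocol article fixes the effect measure: "Multiple regression analysis will be used to calculate OR values for high risk factors", among them lifestyle, clinical and epidemiological variables. On performance it adds that "cut-off values for sensitivity and specificity for predicting occurrence of an aneurysm rupture will be determined by receiver operating curves (ROCs"). Statistical analysis of clinical data gives ANOVA, chi-square and Mann–Whitney tests. Design compares patients who ruptured with those who did not. No section mentions person-time, a time-to-event model or a prediction horizon. Model building refers only to a statistical model, without naming it.

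The timing is set elsewhere:
- Total sample size, for CIAP-1: "1173 patients need to be enrolled per year, that is, 4692 over 4 years".
- Data collection and management: recruitment began in September 2016, and "The estimated primary completion date will be in December 2020". Visits in the first year are followed by visits "at least annually for a minimum of 5 years thereafter". Participation ends at rupture, and deaths are recorded.
- Design and Total sample size: the analysis is in year 5.
- Methods and design: participation does not influence treatment, so aneurysms may be repaired during follow-up.
- Expected loss rate: treatments that could alter the incidence of rupture, and visits outside the time limits, are among the reasons for leaving patients out of the main analysis.
- Model building: a nested comparison samples rupture to non-rupture at 1:2.

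**The concern.** A yes/no analysis needs every patient to be observed for the same period. Here a patient enrolled late and one enrolled at the start enter the regression as the same kind of non-rupture, although the second has been at risk several times as long. Two things follow.

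First, a predicted probability from the model has no period attached. The study's product is meant to support decisions on treating high-risk aneurysms, and a risk without a horizon cannot be set against the risk of treatment.

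Second, any predictor associated with entry date, repair or death carries part of that association into its odds ratio. Aneurysm size and wall enhancement are plausible examples, because they may influence who is repaired and when.

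**Working it through.** **Inputs from the protocol article.** Rupture rate 1% per year; cohort of 5000; 1173 per year over 4 years = 4692; modeling share 2/3; 1:2 nested ratio; loss 20%; at least 130 ruptures in the modeling group in 4 years; 500 to be enrolled; OR 3.05 for wall enhancement. The repair rates below are assumptions and are not in the documents.

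**1. The plan's event count.** The article does not show the derivation. One that fits is 5000 × 0.01 × 4 × 2/3 = 133.3, and then 133.3 × 3 / 0.8 = 500. It gives every patient 4 full years and no loss. With 4692 patients it gives 125.1. With entry spread evenly over 4 years and analysis at year 4, mean follow-up is 2 years and the count is 5000 × 0.01 × 2 × 2/3 = 66.7. With 1 to 5 years of follow-up (mean 3) it is 100. So the planning figure also appears to take follow-up as equal.

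**2. Range of follow-up.** September 2016 to December 2020 is about 4.25 years. With entry over 4 years, follow-up at analysis is a few months to about 4 years, or about 1 to 5 years if the analysis is at the end of year 5.

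**3. Chance of an observed rupture at 1% per year**, 1 − exp(−0.01t):

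| Years at risk | 0.5 | 1 | 2 | 4 | 5 |
|---|---|---|---|---|---|
| Probability | 0.50% | 1.00% | 1.98% | 3.92% | 4.88% |

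Identical patients differ 3.92/0.50 ≈ 8-fold between 6 months and 4 years, and 4.88/1.00 ≈ 5-fold between 1 and 5 years. With follow-up uniform on 0 to 4 years the crude proportion ruptured is 1.97%, against a 4-year risk of 3.92%.

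**4. Odds ratio when follow-up is unrelated to the predictor.** True rate ratio 3.05, follow-up uniform on 0 to 4 years in both groups. Ruptured: 5.86% exposed, 1.97% unexposed. OR = (0.0586/0.9414) / (0.0197/0.9803) = 3.09. The bias is negligible.

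**5. Odds ratio when the exposed are repaired earlier.** Rupture rate λ is 0.0305 exposed and 0.01 unexposed; repair rate r; h = λ + r. The share still unrepaired and unruptured at analysis is S = (1 − exp(−4h)) / (4h). The share with an observed rupture is R = (λ/h)(1 − S).

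Unexposed, r = 0.05: S = 0.889, R = 0.0185.

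| Exposed repair rate | S | R | OR, repaired kept as non-rupture | OR, repaired excluded |
|---|---|---|---|---|
| 10% | 0.779 | 0.0516 | 2.89 | 3.19 |
| 30% | 0.555 | 0.0411 | 2.27 | 3.56 |
| 50% | 0.415 | 0.0336 | 1.85 | 3.90 |

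The fourth column is [R/(1 − R)] divided by the unexposed odds 0.0185/0.9815 = 0.0188. The fifth is (R/S) divided by 0.0185/0.889 = 0.0208. At 30%: 0.0428/0.0188 = 2.27 and 0.0741/0.0208 = 3.56. Excluding repaired patients moves the bias to the other side of 3.05 and does not remove it.

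**The case against.** Several points on the other side stand.

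- **Rare events.** The odds ratio is close to the rate ratio when follow-up and predictor are unrelated (step 4). A reader might infer that every odds ratio in this plan is distorted, or picture a null predictor with a strongly protective OR because its carriers were observed for far less time. The documents give no such split in follow-up, so neither reading is supported.
- **Who counts as non-rupture.** A reader might infer that lost and repaired patients are all scored as non-rupture. Expected loss rate says otherwise: off-schedule patients and those with treatments that affect rupture may be left out of the main analysis. That narrows the point but does not answer it, because the exclusion depends on something that happens after enrolment and discards valid time at risk.
- **Nested sampling.** With 1:2 sampling by outcome an odds ratio is natural, and an unweighted Cox model there would give wrong absolute risks. It estimates a rate ratio if controls are drawn from those at risk at each rupture; no such sampling is stated.
- **Incomplete follow-up.** A reader might see a contradiction in an analysis before the planned years are complete. There is none: the article calls the year-5 results preliminary and plans longer follow-up.
- **Condensed article.** The final model is described only as a statistical model, the quoted sentence concerns life habits and clinical and epidemiological data, and logistic regression is inferred from multiple regression plus odds ratios. But the article does fix the effect measure and the ROC method, so the point concerns a stated choice and not missing detail. The accrual figure is labelled CIAP-1, the cohort from which CIAP-2 is drawn.

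**Conclusion.** The point holds in a limited form. The stated analysis ignores time at risk, which is unequal under either reading of the analysis date. The certain consequence is that predicted probabilities and ROC cut-offs have no defined period: at 1% per year the observed outcome probability varies about 8-fold (6 months against 4 years) or 5-fold (1 against 5 years) between otherwise identical patients. Bias in the odds ratios is conditional. It is negligible without a link between predictor and follow-up. With assumed repair rates of 10% to 50% per year in the exposed against 5% in others, a true 3.05 becomes 2.89 to 1.85 if repaired patients stay in as non-rupture, or 3.19 to 3.90 if they are excluded. These figures rest on constant rates and uniform follow-up of 0 to 4 years; the repair rates illustrate the mechanism and do not forecast what this cohort will show.

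**What to change.** **Full-cohort clinical and imaging predictors.** Replace the odds-ratio regression by a cause-specific Cox model for rupture from enrolment. Censor at repair and at last contact instead of excluding these patients, and treat death from other causes as a competing event when absolute risk is calculated.

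**Horizon and performance.** State a prediction horizon that the year-5 data can support. Report time-dependent AUC and calibration at that horizon in the validation group, in place of the plain ROC.

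**Nested 1:2 part.** Draw non-rupture controls from those still at risk at each rupture time. Use conditional logistic regression, whose odds ratios then estimate rate ratios, or a weighted Cox model. Apply the sampling weights whenever absolute risk is derived.

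**Cost.** Repair dates must be captured; the follow-up items in Data collection and management do not list them. Nested controls must be selected by time at risk, which affects whose samples and images are processed. Otherwise the cost is revised wording and modest extra analysis.

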### Clinical factors are important in predicting rupture of aneurysms

There has been ongoing study of the occurrence and rupture of unruptured aneurysms. Studies have shown that up to 85%–90% of ruptured intracranial aneurysms are ≤ 10 mm in diameter [17–20]. It is inappropriate to recommend treatment for all small (< 7 mm) UIAs because treatment-related morbidity and mortality is close to being higher than the morbidity and mortality of aneurysm rupture. The only published lifelong follow-up study found that smoking and female sex are more serious prognostic factors than aneurysm size [21]. Many factors contribute to SAH, the three predominant risk factors being smoking, sex, and blood pressure [22]. Another prospective study [23] found that old age is also a risk factor for aneurysm rupture. The International Study on unruptured intracranial aneurysms [24] found that the 5-year cumulative rupture rates for patients with no history of SAH with aneurysms located in the internal carotid, anterior communicating, anterior cerebral, or middle cerebral arteries were 0%, 2.6%, 14.5%, and 40% for aneurysms smaller than 7 mm, 7–12 mm, 13–24 mm, and 25 mm or greater, respectively, compared with rates of 2.5%, 14.5%, 18.4%, and 50%, respectively, for the same size categories involving the posterior circulation and posterior communicating artery aneurysms. The location and size of an aneurysm thus have an obvious effect on risk of rupture, as has also been shown in another cohort study [2]. The level of evidence in the above two studies was relatively strong. However, because there was a bias in selection, the external validity of the study needs to be verified; additionally, the applicability of the findings of large studies to the Chinese population is unknown. Some studies in China have found that various morphological features of aneurysms are associated with their rupture. These include irregular morphology of a daughter sac and leaf segments, high aspect ratio (ratio of aneurysm height to neck width), and high size ratio (ratio of aneurysm size to parent artery size). Although these studies have enriched our understanding of factors influencing the risk of rupture of aneurysms, some of them are small single center and/or retrospective studies and thus provide a low level of evidence-based data. More importantly, at present, China does not have a high-level prediction model that integrates these factors. Thus, we plan to carry out a large prospective multicenter cohort study with wide coverage to investigate rupture-related factors in China.

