### Design

Individuals in the UIA follow-up cohort will be allocated to two groups, a modeling and a validation group, in a ratio of 2:1. Taking the annual rupture rate as 1% [2], the rate of loss would be less than 20%. The data will be analyzed statistically in the 5th years, the expectation being that at least 130 patients’ aneurysms will rupture in the first 4 years. The modeling group will be used to establish the risk of UIA rupture and compare relevant clinical information, radiological images, hemodynamic variables, genetic factors, HRMRI findings, and biomarkers [12, 13, 26–37] between the rupture and non-rupture groups to identify the risk factors for rupture. These will then be incorporated into a multi-dimensional model for predicting risk of UIA rupture. The validation group will then be used to validate that model (Fig. 2).

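### Odds ratios and ROC cut-offs are the only measures named for a model meant to inform treatment; neither checks absolute risk, and neither would reveal inflation from an uncorrected 1:2 nested sample

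*Protocol article*

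**What the plan says.** In *Evaluation of risk factors for aneurysms*, the article plans multiple regression to obtain odds ratios, and then: "cut-off values for sensitivity and specificity for predicting occurrence of an aneurysm rupture will be determined by receiver operating curves (ROCs". The model is next applied to the validation group to judge how well it works, and may be adjusted afterwards. No measure is named for that step.

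The purpose is stated in the abstract's *Methods*: "the resultant evidence-based prediction will provide a preliminary theoretical basis for treating aneurysms at high risk of rupture". The rupture rate assumed in *Design* and *Total sample size* is 1% per year.

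Two data structures are described. In *Design*, the follow-up cohort is to be "allocated to two groups, a modeling and a validation group, in a ratio of 2:1". In *Model building*, differences in hemodynamic variables, genes and biomarkers are analyzed in a nested sample with two non-ruptured aneurysms for each ruptured one. The article does not say which of the two supplies the coefficients and intercept of the final model.

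**The concern.** A treatment discussion needs the probability that an aneurysm ruptures within a stated time. Odds ratios rank factors, and sensitivity and specificity describe how well the model separates ruptured from unruptured aneurysms. None of them depends on how common rupture is, and none compares predicted with observed risk. A model can therefore do well on every measure named here while its predicted risks are wrong by a large factor.

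The protocol's own design makes this more than a theoretical worry. Sampling by outcome at 1:2 raises the event share far above that of the cohort. If the model is fitted there and the intercept is left uncorrected, every predicted risk is too high, and nothing named in the article would reveal it.

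**Working it through.** **The plan's own figures.** *Total sample size* says that "at least 130 aneurysms are expected to rupture in the modeling group in the first 4 years". With 5000 patients, a two-thirds modeling share and 1% per year for 4 years:

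- 5000 × 2/3 × 4 × 0.01 = 133.3, or 5000 × 2/3 × (1 − 0.99⁴) = 131.3. The figure of 130 is reproduced, but only with no loss and 4 full years for everyone. With 20% loss, 133.3 × 0.8 = 106.7.
- The 500 is consistent with the 1:2 sample: 130 ruptures plus 260 non-ruptures is 390, and 390 / 0.8 = 488. The article does not show this derivation, so it is my reading.

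**Event share.**

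- Cohort over 4 years: p = 1 − 0.99⁴ = 0.0394; odds = 0.0394 / 0.9606 = 0.0410.
- Nested sample at 1:2: p = 1/3; odds = 0.50.
- Ratio of odds: 0.50 / 0.0410 = 12.2.

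Cross-check by sampling fraction: the modeling group has about 3333 − 131 = 3202 non-ruptures, of which 2 × 131.3 = 262.7 would be sampled. 3202 / 262.7 = 12.2.

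In a logistic model, sampling on outcome alone leaves the odds ratios unchanged and shifts the intercept by ln 12.2 = 2.50. Uncorrected, an aneurysm with a true 4-year risk of 3.9% would be given 33%. One with a true risk of 1% would be given 0.0101 × 12.2 = 0.123 in odds, that is 11%. Adding a constant to every patient's log-odds does not change their order, so the ROC curve, the AUC and the attainable pairs of sensitivity and specificity stay the same.

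The factor depends on follow-up. If staggered entry cut the event share to about 2%, it would be 0.50 / (0.02 / 0.98) = 24.5.

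**Predictive value.** PPV = se·p / [se·p + (1 − sp)(1 − p)]. The documents give no sensitivity or specificity for the model, so a range is assumed.

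| Sensitivity / specificity | PPV, cohort (p = 0.0394) | PPV, 1:2 sample (p = 1/3) |
|---|---|---|
| 70% / 70% | 8.7% | 53.8% |
| 80% / 80% | 14.1% | 66.7% |
| 90% / 90% | 27.0% | 81.8% |

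Within each row, sensitivity and specificity are the same in both settings, while PPV differs by a factor of 3 to 6.

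**The case against.** The strongest reply is that this is a condensed article. Performance measures for a validation step are often left to the analysis plan, which is not shown and may well include calibration. That stands as a limit: the article cannot be faulted for leaving detail out. What remains open to comment is what it does fix, namely odds ratios and ROC-based cut-offs, for a purpose that turns on absolute risk.

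Several stronger readings are tempting and are not supported.

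- *That the evaluation could not expose the problem.* Validation is planned in the second part of the follow-up cohort. If that is the unselected third, with no loss it holds about 1667 patients and, at 4%, 67 ruptures. At 80%/80% there would be about 53 true and 320 false positives, which can be counted. The wording used for judging the model is undefined, not restricted to ROC measures.
- *That the cut-off rule ignores prevalence and weighs one missed rupture as about 24 false labels.* The 24 is (1 − p)/p = 0.9606 / 0.0394, and it holds only for a Youden cut-off with a calibrated model. The article names no criterion, and a ROC cut-off can be chosen with prevalence or cost weights.
- *That a low PPV is itself an error.* It comes mainly from the low event rate. At 80% sensitivity and a 4-year risk of 4%, a PPV of 50% needs a specificity of about 97%, however the cut-off is chosen. A flagged group at 14% against 4% overall is useful stratification.
- *That the Background sets the opposite balance of harms.* It says that "treatment-related morbidity and mortality is close to being higher than the morbidity and mortality of aneurysm rupture", as a reason not to treat every small aneurysm. That is near parity for untargeted treatment of one size class, not a statement about aneurysms flagged by a model.
- *That the ROC cut-off is a treatment rule.* The sentence follows the odds ratios and may concern single predictors, and the abstract promises only a preliminary basis for treatment.

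**Conclusion.** The point holds in a limited form. The only measures the article names do not reflect the rupture rate and do not check predicted against observed risk, although the model is meant to inform treatment. That is a poor match of measure to purpose, and it is cheap to correct.

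The size depends on a condition that the article leaves open. If terms are fitted in the 1:2 sample without correction, predicted odds are about 12 times too high, assuming 1% per year, 4 full years of follow-up and sampling on outcome only. Assessing performance in that sample as well would show a PPV of 67% instead of about 14% at an assumed 80%/80%. If the model is fitted and validated in the unselected cohort, this inflation does not arise, and what remains is only that calibration and predictive values should stand beside the ROC results. A reader might infer that the nested sample certainly supplies the final model; the text does not say so.

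**What to change.** In *Evaluation of risk factors for aneurysms*:

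1. Express the model output as absolute predicted risk of rupture at a stated horizon, for example 4 years.
2. State which data fit each term. If the nested sample is used, correct to the cohort rupture rate, by adjusting the intercept for the sampling fraction or by weighting the sampled non-ruptures.
3. In the validation part of the follow-up cohort, report the observed/expected ratio, calibration slope and calibration plot, and PPV and NPV at any cut-off shown, alongside the ROC curve and AUC. If some predictors are measured there only in a sampled subset, apply the same weighting.
4. A decision curve over a range of thresholds is optional. No clinical threshold needs to be set in this analysis.

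The cost is some wording and extra output, plus a record of the sampling fractions if the nested sample is used. The headline becomes less simple than a single cut-off.

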## Background

Intracranial saccular aneurysms are increasingly often being detected in clinical practice in parallel with the increasing frequency of performing computed tomography (CT) and magnetic resonance imaging (MRI). A recent cross-sectional study of community data showed that the prevalence of unruptured intracranial aneurysm (UIA) is as high as 7% [1] among 35–75-year-old individuals in China. The rate of rupture of such aneurysms was almost 1% in a Japanese study [2]. Although the incidence is low, the consequences of aneurysm rupture are serious, the mortality rate in the early stages of hemorrhage reportedly being 40% and the rebleeding rate as high as 60%–70% [2]. Some models for predicting enlargement and rupture of such aneurysms are currently available. However, one of these models is for assessing risk of rupture of bifurcation aneurysms and incorporates only a few indicators [3]. Another large study had some bias that made the external efficiency relatively low [4]. These results and models are difficult to incorporate into clinical practice. It is therefore essential to identify all risk factors and construct a more accurate model for predicting rupture of aneurysms in Chinese people that is simpler to use and more effective in clinical practice.

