Risk factors for rupture, including hemodynamic variables, genes, and biomarkers will be calculated in a nested cohort study of the entire first cohort (CIAP-1: the first project of the China Intracranial Aneurysm Project and is managed by Tangdu Hospital, Fourth Military Medical University). A multi-dimensional model for predicting UIA rupture and bleeding that incorporates clinical, imaging, HRMRI data, and so on will be constructed by using a statistical model.Model validation: After establishment of the model, the second group of the follow-up cohort will be used for blind verification.Comparative analyses of histopathology of aneurysm walls: When participants undergo surgery for ruptured intracranial aneurysms, the sites of rupture will be identified intraoperatively and specimens of the aneurysm wall will be removed and preserved in formalin. The location of rupture, pathological damage, hemodynamic variables, HRMRI findings, and relevant biomarkers will be analyzed to identify differences between unruptured and unruptured aneurysms. Relationships between pathological damage, hemodynamic variables, and HRMRI features of the aneurysm wall will also be assessed.

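### Validation tests only the combined model's own accuracy, so it cannot show that HRMRI, hemodynamic, genetic and biomarker data improve on known clinical and morphological factors

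*Protocol article*

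**What the plan says.** The Background of the protocol article criticises existing rupture models, one of them for using few indicators, and sets out to "construct a more accurate model for predicting rupture of aneurysms in Chinese people". The Design and Model building sections name what is added: HRMRI findings, hemodynamic variables, genetic factors and biomarkers, alongside clinical and imaging data.

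The evaluation is described in three places.
- Design: the follow-up cohort is "allocated to two groups, a modeling and a validation group, in a ratio of 2:1", and "The validation group will then be used to validate that model".
- Model building: "the second group of the follow-up cohort will be used for blind verification".
- Evaluation of risk factors for aneurysms: multiple regression gives odds ratios and ROC curves give cut-offs. Then "Next, the model will be used to assess risk of aneurysm rupture in the validation group", to establish its efficacy and accuracy. The sequence ends: "Finally, the model will be adjusted as indicated and established".

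The section on clinical factors states: "The location and size of an aneurysm thus have an obvious effect on risk of rupture". Size, location, shape and aspect ratio are listed among the model's inputs under Model building.

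**The concern.** The motivation is comparative and the evaluation is not. The validation result depends on two things: the combined model's predictions and who ruptured. The accuracy of a model without the new data does not enter. If the combined model does well, two explanations remain open: the new data help, or size, location and the other known factors work as they already did. The described analysis cannot separate them.

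The abstract says the resulting prediction should give a preliminary basis for treating high-risk aneurysms. HRMRI, flow simulation and genetic testing could be credited with predictive value that comes from factors already in routine use.

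**Working it through.** **1. Event counts.** Total sample size expects at least 130 ruptures in the modeling group within 4 years. This reproduces approximately as 5000 × 1% × 4 × 2/3 = 133 with no loss; with 20% loss it is 107. At the 2:1 split, 130 modeling ruptures imply 130/2 = 65 in validation. The Design section can be read as giving 130 for the whole cohort, which leaves 130/3 ≈ 43. If only the 500 CIAP-2 patients were followed, 500 × 1% × 4 = 20 ruptures (16 after 20% loss), so 5 to 7 in validation.

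**2. How far known factors separate risk.** The section on clinical factors quotes 5-year rupture rates of 0, 2.6, 14.5 and 40% by size for anterior sites, and 2.5, 14.5, 18.4 and 50% for posterior and posterior communicating sites. AUC = sum over pairs of size-by-location cells of P(cell i | rupture) × P(cell j | no rupture), counted 1 if rate i exceeds rate j and ½ if equal. The case mix is not in the article. Assuming 60–90% of aneurysms under 7 mm and 15–45% at posterior sites, the AUC is 0.85–0.94.

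That range should not be taken at face value. Assume a size mix of 60/25/12/3% and 20% posterior:
- under 7 mm: 0.60 × 0.20 × 0.025 = 0.0030
- 7–12 mm: 0.25 × (0.80 × 0.026 + 0.20 × 0.145) = 0.0125
- 13–24 mm: 0.12 × (0.80 × 0.145 + 0.20 × 0.184) = 0.0183
- 25 mm or more: 0.03 × (0.80 × 0.40 + 0.20 × 0.50) = 0.0126

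The total is 0.0464, so (0.0030 + 0.0125)/0.0464 = 33% of ruptures arise at 12 mm or less. A mix of 85/11/3/1% with 35% posterior gives (0.0074 + 0.0074)/0.0240 = 62%. The same section says that 85–90% of ruptured aneurysms are 10 mm or smaller. Lower clinical AUCs, 0.65 to 0.80, are therefore used below.

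**3. Validation when the new markers carry no information.** Assumptions:
- one normal clinical score with the stated AUC
- ten independent noise markers, all forced into a logistic model
- 1:2 rupture to non-rupture, the ratio given under Model building
- success if the lower DeLong 95% limit of the validation AUC exceeds 0.5

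| Ruptures, modeling/validation | AUC 0.65 | 0.70 | 0.75 | 0.80 |
|---|---|---|---|---|
| 130/65 | 0.81 | 0.99 | 1.00 | 1.00 |
| 87/43 | 0.60 | 0.91 | 0.99 | 1.00 |
| 60/30 | 0.39 | 0.74 | 0.92 | 0.996 |

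The entries are proportions of 1000 simulated runs that succeed; repeat runs agreed to within about 0.04. With only 5 to 7 validation ruptures, a score with a true AUC of 0.70 succeeds in 0.43–0.50 of runs, and one of 0.85 in 0.87–0.95.

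**4. With the screening that the plan describes.** The article compares factors between rupture and non-rupture groups at P < 0.05 before building the model. Screening the ten noise markers this way leaves none of them in about 56–60% of runs. At 130/65 ruptures the success rate is then about 0.91–0.95 across repeat runs at clinical AUC 0.65, and about 1.00 at 0.70 and 0.75. Screening does not lower the rate at which an uninformative set of markers ends in a validated model.

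**5. The paired comparison.** Apply the clinical-only and combined models to the same validation patients and require the lower 95% limit of the AUC difference to exceed zero. Uninformative markers then succeed in under 1% of runs. If the two odds ratios in Total sample size are real (3.05 and 4.7, assumed independent, each marker at 30% prevalence), the AUC gain is about 0.05–0.13. Power is 0.63–0.88 with 65 validation ruptures and 0.41–0.69 with 43.

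**The case against.** The strongest reply is that this is an omission in a condensed article: a comparator, an incremental test and a pass rule can sit in an analysis plan that is not shown. That holds for thresholds and test details, and the point does not rest on their absence. It rests on the article setting out an evaluation sequence, in three places, that does not address its own motivation.

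A second reply is that greater accuracy appears in the Background, set against published models, while the Aims section speaks only of exploring risk factors and developing a multidimensional model. This is fair. Greater accuracy is the motivation and not a formally stated objective, and a clinical-only reference model would not settle the contrast with published scores. It would show whether the added data contribute, which is the reason given for collecting them.

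Adjusted odds ratios from the multiple regression do not fill the gap. They describe association in the modeling group, not better prediction in new patients.

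Several stronger readings are tempting but not supported.
- *The model would validate almost surely whatever the markers do.* The article states no pass rule; the AUC criterion is an assumption, and step 3 shows rates well below 1 with a clinical AUC of 0.65 or few ruptures.
- *Adding useless markers would make the model clearly worse.* At clinical AUC 0.75 and 130/65 ruptures, forced entry gives a mean AUC of 0.735 against 0.752, but screening gives 0.748 against 0.752. Most of the loss comes from leaving out the screening.
- *Size and location alone reach an AUC near 0.9.* The implied size distribution of ruptures conflicts with the article's own figure (step 2), and the article also notes selection bias in that source.
- *Validation rests on ROC performance alone.* ROC curves are tied to the cut-offs; the validation measure is given only as efficacy and accuracy.

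**Conclusion.** The point holds in limited form. As described, validation cannot show that HRMRI, hemodynamic, genetic or biomarker data improve prediction beyond factors the article already accepts as predictive. This follows from the text and needs no simulation.

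The size is conditional. It assumes the AUC criterion above, independent uninformative markers, a clinical AUC of 0.70 or more and about 65 validation ruptures. The false impression of success then arises in about 99% of runs or more. With about 43 validation ruptures and a clinical AUC of 0.70 it is 91% under forced entry.

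The documents do not support saying that the combined model will be worse than a clinical one, or that costly testing will be recommended as a result.

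**What to change.** Under Evaluation of risk factors for aneurysms, add a reference model fitted in the modeling group from the clinical and routine morphology factors listed under Model building (age, sex, blood pressure, smoking, size, location, aspect ratio and so on). Apply it and the combined model to the same validation patients, restricted to those with marker data. Report the paired AUC difference with its 95% confidence interval and a likelihood-based measure of added information, beside the combined model's own accuracy.

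Claim better prediction from the added data only if that interval supports it. Otherwise state that added value was not shown. Given the power in step 5, there should be no rule that the simpler model must then replace the combined one: a useful marker set could miss the criterion.

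The cost is one further model fit and a paired comparison. Marker data in validation patients are needed, but validating the combined model needs them anyway. The article should say where they come from, because 130 modeling ruptures with two controls each and 20% loss already give 130 × 3/0.8 = 487.5, close to the whole 500. The downside is that the difference will be imprecise and probably less favourable than the stand-alone AUC.
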